### Outcomes

**
*Primary and secondary*
**

The primary outcome is SHS exposure at homes at 10 months and 16 months as assessed by the change in mean urine cotinine levels among women and or children of the smoker at the individual level. The secondary outcomes will include individual level self-reports of smoking within homes, particulate matter 2.5, harm reduction (reduction in the number of cigarettes smoked), quitting of smoking, blood pressure, Fagenstrom Nicotine dependence score, and comorbidities. Individual level assessment of Fev1/Fev6 will also be carried out with handheld spirometry considering a cut off of 73% to be indicative of COPD which is also a secondary outcome. Forced expiratory volume in 1 second (FEV1) is the maximum amount of air that the subject can forcibly expel during the first second following maximal inhalation.
^
46
^ Similarly, forced expiratory volume in 6 seconds (FEV6) is the volume of forcibly exhaled air measured during 6 seconds
^
47
^ which can be measured by handheld spirometry.

Cluster level assessment of 2.5 particulate matter in homes will also be done with air quality monitors. Monitoring and assessing intervention in terms of development of a training booklet, educational material, number of meetings organized, proportion of self-help group members in the area participating and inviting local self-government members to participate.

In order to understand the reasons for success and failure, in-depth interviews of men who have successfully quit smoking within homes, quit smoking completely, ASHAs, and health workers will be conducted. Focus group discussions of wives of smokers who quit smoking within homes and those who reduced the number of cigarettes will be conducted.

*Data analysis and statistical plan*: Data will be entered electronically on a secure file storage system and password protected. Data will be anonymised by assigning a unique identification number to each smoker. Outcome data will be reported in accordance with the Standard Protocol Items: Recommendation for Intervention Trials (SPIRIT). All the smokers will be included in the analysis regardless of reduction in smoking within homes.

**
*Participant flow*
**

30 clusters will be randomly assigned into two groups and will receive intended intervention and will be analyzed for primary outcome of urinary cotinine. For each group losses and exclusion of clusters and individual participants will be recorded (
Figure 1).

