*Baseline data*: The baseline data will be presented for both clusters and individuals as the risk of chance imbalances are greater with clusters.

*Numbers analyzed*: We plan to analyze 30 clusters with at least 300 indoor smokers in each arm. The urine cotinine of the women and children will be obtained from 300 women and or children in each arm. The indoor home values of 2.5 PM will be obtained from 300 households in each arm. Similarly, the lung function values as indicated by FeV1/FeV6 will be assessed among 300 each in the intervention and control group.

*Outcomes and estimation*: The difference in mean cotinine levels among the clusters in the intervention and control group with 95% CI will be estimated. The intracluster correlation coefficient for each outcome will be reported. Adjusted estimates of clustering will also be provided. Cox’s proportional hazards will be calculated for quitting, harm reduction, blood pressure values. This is to determine the effectiveness of an intervention based on partnering with women’s SHG’s to reduce indoor tobacco smoking by measuring urinary cotinine levels.

A repeated-measures ANOVA will be used to compare the mean urinary cotinine concentration between groups, before and after intervention.

Analysis for self-reported quit rates will be assessed by a Cox proportional hazards model. Generalised linear mixed effect models will be used to test between cluster differences from baseline to each follow up period for each outcome indicator.

We will use an intention to treat approach in analysis. A multilevel model will be used for analysis using the generalized linear mixed effect model which will also adjust for individual covariates. Key variables will be measured at baseline and then compared between arms to check balance; and if both arms are unbalanced with respect to any relevant factors, which can happen given that the unit of randomization is the cluster instead of the individual, those factors will be adjusted for in the final analysis so as to address potential confounding. Analysis for SHS exposure rates and quit rates will be assessed by a Cox proportional hazards model.

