•To correlate the urinary cotinine levels with the second-hand smoke in the home environment: correlation and linear regression analysis will be carried out by Pearson’s correlation if it follows a normal distribution and Spearman if it is a non-normal distribution.The difference in cotinine levels will be analysed by comparing the urine level of cotinine at the end of follow up, adjusted for the baseline value, by using linear mixed model or GEE to allow for cluster effect.•To measure the effectiveness of the intervention among smokers by measuring their FeV1/FeV6 using COPD6.To determine the effectiveness of the intervention in improvement of lung function the ratio of FeV1/FeV6 will be measured pre- and post-intervention and the mean difference between the groups will be assessed by a paired t-test.
**
*Qualitative data analysis*
**

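### The mixed-model sentence for the outcome indicators names a between-cluster difference from baseline, when the trial needs a between-arm difference adjusted for each outcome's baseline value

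*Protocol article*

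**What the plan says.** All of this is in the Outcomes section of the protocol article, mostly under Outcomes and estimation.

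- For every outcome: "Generalised linear mixed effect models will be used to test between cluster differences from baseline to each follow up period for each outcome indicator".
- The next paragraph adds a general model: "A multilevel model will be used for analysis using the generalized linear mixed effect model which will also adjust for individual covariates". The covariates are not named. If the arms are unbalanced on relevant factors at baseline, "those factors will be adjusted for in the final analysis so as to address potential confounding".
- Cotinine is described in three ways. The primary outcome is "the change in mean urine cotinine levels among women and or children of the smoker at the individual level". Under Outcomes and estimation, "A repeated-measures ANOVA will be used to compare the mean urinary cotinine concentration between groups, before and after intervention". Under the correlation aim, the analysis is "comparing the urine level of cotinine at the end of follow up, adjusted for the baseline value, by using linear mixed model or GEE".
- For some secondary outcomes: "Cox’s proportional hazards will be calculated for quitting, harm reduction, blood pressure values".

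Table 1 shows PM2.5, blood pressure, the nicotine dependence score and daily cigarettes measured at baseline and at both follow-ups. Quitting has no baseline entry.

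**The concern.** There are three linked problems.

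**The contrast.** In a mixed model for a cluster trial, differences between clusters are variation among slums. The treatment effect is the difference between arms, and the sentence that covers every outcome does not name it.

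**The use of baseline.** A difference from baseline to follow-up is usually fitted as a change score, or as an arm-by-visit contrast with baseline as one of the responses and its mean free in each arm. With complete data both target the same quantity: the between-arm difference at follow-up minus the between-arm difference at baseline. That subtracts the whole baseline difference, whereas regression to the mean calls for only part of it. The result is extra variance and over-correction of any chance baseline difference. The article itself warns that chance imbalance is a greater risk with clusters.

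**Inconsistency.** The better analysis is written out for cotinine only. PM2.5, which belongs to the first aim, and the nicotine dependence score have only the general wording. Blood pressure and cigarette reduction have that wording and a Cox model.

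At stake is the precision and clarity of the secondary comparisons. PM2.5 comes from a single recording of 6 to 8 hours per survey (Data collection), so a low baseline to follow-up correlation is plausible for it.

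**Working it through.** **1. The plan's own figure (Sample size calculation).** Inputs: 113 per arm, 20 per cluster, ICC 0.06, CV 0.45, dropout 10%.

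- VIF = 1 + ((0.45² + 1) × 20 − 1) × 0.06 = 1 + 23.05 × 0.06 = 2.383, stated as 2.4.
- 113 × 2.4 = 271.2, stated as 271. 271 / 20 = 13.55, so 14 clusters.
- 271 / 0.9 = 301 and 271 × 1.1 = 298, rounded in the plan to 300, which is 15 clusters of 20.

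The calculation reproduces. It concerns cotinine only, and nothing below changes it.

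**2. Variances.** Assumptions, because the article gives neither: r is the baseline to follow-up correlation of individuals within a slum, and p is the correlation of slum effects over time (persistence). Take ICC 0.06 and 20 × 0.9 = 18 analysed per slum, with equal slum sizes.

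- Variance of a slum mean: V = 0.06 + 0.94/18 = 0.1122. Slum effects make up 0.06/0.1122 = 53% of it, so p matters as much as r.
- Correlation of slum means: ρ = (0.06p + 0.0522r) / 0.1122.
- Relative to follow-up alone (1), the change analysis has variance 2(1 − ρ). Adjustment that includes the slum-mean baseline has 1 − ρ². The ratio is 2/(1 + ρ).

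| p | r | ρ | Change | Adjusted | Ratio |
|---|---|---|---|---|---|
| equal to r | 0.3 | 0.300 | 1.40 | 0.91 | 1.54 |
| equal to r | 0.5 | 0.500 | 1.00 | 0.75 | 1.33 |
| equal to r | 0.7 | 0.700 | 0.60 | 0.51 | 1.18 |
| equal to r | 0.9 | 0.900 | 0.20 | 0.19 | 1.05 |
| 0.8 | 0.3 | 0.567 | 0.87 | 0.68 | 1.28 |
| 0.8 | 0.5 | 0.660 | 0.68 | 0.56 | 1.20 |
| 0.8 | 0.7 | 0.753 | 0.49 | 0.43 | 1.14 |
| 1.0 | 0.3 | 0.674 | 0.65 | 0.55 | 1.19 |
| 1.0 | 0.7 | 0.860 | 0.28 | 0.26 | 1.08 |

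**3. Check by simulation.** The formula ignores the cost of estimating the slope from 30 slums. With 15 slums of 20 per arm, p = 0.8 and 4,000 trials per setting, adjustment for the slum-mean baseline gave ratios of 1.21, 1.16 and 1.09 at r = 0.3, 0.5 and 0.7. The formula for 20 per slum gives 1.27, 1.20 and 1.14. The real gain is therefore somewhat below the formula.

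**4. Individual baseline value only.** If the model carries only the individual value, its slope is close to r and the relative variance is about 1 + r² − 2rρ. At r = 0.3:

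- p = 0.8: 1 + 0.09 − 0.340 = 0.750. Ratio 0.865/0.750 = 1.15 (simulated 1.14).
- p = 1.0: 1 + 0.09 − 0.405 = 0.685. Ratio 0.651/0.685 = 0.95 (simulated 0.97).

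When slum effects are fully stable, adjusting for the individual value alone gains nothing over change. The slum mean has to be in the model as well.

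**5. Illustrative power.** The 113 per arm implies a standardised difference of √(2 × (1.960 + 0.842)² / 113) = 0.373. With 271 per arm, VIF 2.4, r = 0.3 and p = r:

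- Change: SE = √(2 × 2.4 × 1.40/271) = 0.157, power 66%.
- Adjusted: SE = √(2 × 2.4 × 0.91/271) = 0.127, power 83%.
- At r = 0.7 the same calculation gives 95% and 97%.

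This is the cotinine effect size, and the secondary outcomes were not sized on it.

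**The case against.** The strongest case against is that the article fixes no change score. A mixed model for differences from baseline can carry the baseline value as a covariate or constrain the baseline means to be equal across arms, and then no precision is lost. The following paragraph adds individual covariates and an imbalance rule, neither limited to cotinine. The exact response and covariate list are normally left to a statistical analysis plan. A change analysis is also unbiased under randomisation.

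Much of this stands. A reader might infer that the secondary outcomes will certainly lose precision, or that baseline adjustment is reserved for cotinine. The text supports neither: no sentence excludes the baseline value, and cotinine falls under the same general sentence as well as a repeated-measures ANOVA.

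A reader might also infer two general rules: that change is never more precise than a baseline-adjusted analysis, and that below r = 0.5 it is worse than ignoring baseline. Both assume that slum effects persist no more than individual values. At r = 0.3 and p = 0.8, change has 0.87 times the variance of follow-up alone. At p = 1.0 it matches or slightly beats a model with the individual baseline only.

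What does not stand is that the other wording cures the sentence. Unnamed covariates, and adjustment triggered by observed imbalance, do not commit to each outcome's own baseline. Nor is this only absent detail. The contrast is stated, it is the wrong one, and it sits beside a different analysis for cotinine and Cox models for two other outcomes.

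**Conclusion.** The point holds as a defect of wording and consistency, with a probable but unquantified loss of precision. The general sentence should name the between-arm contrast and use each outcome's baseline value. PM2.5 and the nicotine dependence score depend on it most. Blood pressure and cigarette reduction have two stated methods that must be reconciled.

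If the sentence is implemented in the ordinary way, the variance excess is about 50% at r = 0.3 with p = r. It is about 20% to 30% at r = 0.3 with p from 0.8 to 1.0, against a model that also uses the slum-mean baseline, and about 5% at r = 0.9 with p = r. These figures rest on ICC 0.06, 18 per slum, equal slum sizes and assumed r and p. If the model already carries both baseline terms, the loss is zero.

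A reader might infer that the trial is underpowered or its primary result biased. Neither follows. The sample size reproduces, it concerns cotinine, and cotinine has a baseline-adjusted analysis in the text, although its other descriptions should be aligned with it.

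**What to change.** Replace the general sentence with: *For each continuous or count outcome measured at baseline, the follow-up value is the response in a mixed model with arm, visit, arm-by-visit, that outcome's own baseline value (individual value and slum mean) and a slum random effect; the reported effect is the between-arm difference at each follow-up.*

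Then:

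- Define the primary effect for cotinine to match the analysis already described as "comparing the urine level of cotinine at the end of follow up, adjusted for the baseline value", and say what role, if any, the repeated-measures ANOVA keeps.
- State one method each for blood pressure and cigarette reduction, resolving the conflict with the Cox models.
- Compare outcomes without a baseline value, such as quitting, directly between arms.

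The cost is analysis wording only, because Table 1 already schedules the baseline measurements. The article reports baseline collection as ongoing with allocation to follow, so on that status the change can be made before any follow-up data exist.

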### Sample size calculation

Based on previous studies we assume an ICC of 0.06.
^
43
^ To detect a minimal difference of 0.03ng/ml in cotinine levels between groups,
^
44
^ at 80% power with a two-sided alfa of 0.05, the estimated sample size was 113 indoor smokers per arm for individual randomization. Since one of the studies in the slum area of Ernakulam had found a prevalence of indoor smoking of 16% and considering slums above 100 households it is assumed that the expected number of smokers within household will be 20 per cluster with variability in clusters. Hence we estimated the sample size for unequal cluster size,
^
45
^ with a CV of 0.45 and VIF=2.4. The estimated sample size was 271 and 14 clusters per arm. Further we assumed a drop-out rate of 10%, the final sample size was rounded to 300 per arm and 15 clusters.

**
*Randomisation*
**

The trial has been registered in Clinical Trials Registry – India
CTRI/2021/06/034478.

A simple randomisation will be undertaken of the selected slums in the urban and peri-urban areas to receive intervention or not by a computer-generated random number list.

Allocation concealment: Allocation will be based on clusters and the allocation will be done after the baseline survey assessment by a statistician not directly related to the study. There is no allocation concealment. All the indoor smokers will be recruited and they will be selected before randomising clusters.

*Implementation*: Meetings will be conducted with the Kochi Corporation and District Medical Office regarding the objectives of the study. After the baseline survey, which will help to identify the indoor smokers, smoking practices, ventilation issues, and waste management practices, a simple randomisation will be undertaken of the selected slums in the urban and peri-urban areas to receive intervention or not.

The allocation sequence generation and the assignment of participants to the intervention will be carried out by the statistician and the investigators will enrol the participants.

*Blinding*: Blinding may not be possible as a lot of people are involved, local self-government officials, the investigators team, health centres, health workers, frontline workers such as the accredited social health activist, and anganwadi workers. The group of people who collect the outcome data will be blinded.

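### Beyond baseline cotinine and unnamed individual covariates, further adjustment is triggered by observed imbalance between arms; a short list of prognostic covariates fixed before allocation should replace that trigger

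*Protocol article*

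**What the plan says.** All of this is in the protocol article, Methods.

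- **The trigger** (Outcomes, under Outcomes and estimation): "Key variables will be measured at baseline and then compared between arms to check balance". Then, "if both arms are unbalanced with respect to any relevant factors", "those factors will be adjusted for in the final analysis so as to address potential confounding". The text does not say which variables are key, how imbalance is measured, or how large it must be.
- **Unconditional adjustment, first statement** (same paragraph): the multilevel analysis uses a "generalized linear mixed effect model which will also adjust for individual covariates". The covariates are not named, and no condition is attached.
- **Unconditional adjustment, second statement** (the analysis bullets that follow): cotinine at the end of follow-up is "adjusted for the baseline value, by using linear mixed model or GEE to allow for cluster effect".
- **Another analysis of the same outcome** (Outcomes and estimation): "A repeated-measures ANOVA will be used to compare the mean urinary cotinine concentration between groups, before and after intervention". No covariates are mentioned for it.
- **Allocation** (Randomisation, under Sample size calculation): "A simple randomisation will be undertaken of the selected slums in the urban and peri-urban areas", and "the allocation will be done after the baseline survey assessment by a statistician not directly related to the study". No stratification, matching or constraint is stated.

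**The concern.** Under randomisation, baseline differences between arms arise by chance. Covariate adjustment helps to the extent that the covariate predicts the outcome. A factor that strongly predicts cotinine is worth including even when the arms match on it. A factor that predicts little is not worth including because the arms happen to differ. A rule keyed to observed difference can get both cases wrong.

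The design makes this relevant. Only 30 clusters are allocated, by simple randomisation, across urban and peri-urban slums, and the article itself (Baseline data) recognises that chance imbalance is a greater risk with clusters. Balance can be examined only after allocation, and nothing fixes the resulting model before outcomes are known. At stake are the precision of the primary comparison, its error rate in the particular allocation obtained, and the analyst's freedom to choose which covariate set produces the primary result.

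**Working it through.** **Inputs from the article:** 15 clusters and 300 participants per arm, mean cluster size 20, CV of cluster size 0.45, ICC 0.06, 113 per arm under individual randomisation, 10% drop-out (all from Sample size calculation); 1:1 allocation (Sample selection).

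**Assumptions, not in the article:** where a test is needed, unbalanced means p < 0.05 on a t-test with 28 df; the correlation r between covariate and outcome is 0.3, 0.5 or 0.7.

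**1. The plan's own figures reproduce.**
- VIF = 1 + ((CV² + 1) × m − 1) × ICC = 1 + (1.2025 × 20 − 1) × 0.06 = 2.383, stated as 2.4.
- 113 × 2.4 = 271.2, and 271/20 = 13.55, so 14 clusters.
- 271/0.90 = 301, stated as 300 and 15 clusters.

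The point below does not alter these figures.

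**2. Chance imbalance in a cluster-level factor.**
- SE of the standardised difference = √(2/15) = 0.365 SD.
- P(|difference| > 0.25 SD) = 49%; P(|difference| > 0.5 SD) = 17%.
- Smallest difference flagged at 5% = 2.048 × 0.365 = 0.75 SD.
- Simulation (400,000 allocations): the test would miss 90% of differences above 0.25 SD and 71% of those above 0.5 SD.

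**3. Chance imbalance in an individual-level factor, ICC 0.06.**
- SE = √(2 × 2.383/300) = 0.126 SD.
- Smallest difference flagged = 2.048 × 0.126 = 0.26 SD (0.19 to 0.40 SD for ICC 0.01 to 0.20).
- P(> 0.25 SD) = 4.7%; P(> 0.5 SD) = about 0.01%.

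The problem of missed imbalance is therefore mainly one of cluster-level factors.

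**4. Consequences for the analysis.** Simulation on cluster summaries, 15 against 15, one prognostic covariate, 40,000 trials per row, no true effect. A missed imbalance is a non-significant difference above 0.5 SD, which occurs in about 12% of trials.

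| r | Type I error, rule | Type I error, fixed adjustment | Rule, missed imbalance | Fixed, missed imbalance | SE, rule | SE, fixed |
|---|---|---|---|---|---|---|
| 0.3 | 4.7% | 4.9% | 6.3% | 4.9% | 0.362 | 0.354 |
| 0.5 | 4.3% | 4.8% | 9.1% | 5.0% | 0.352 | 0.321 |
| 0.7 | 3.7% | 5.0% | 12.3% | 5.3% | 0.343 | 0.267 |

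At r = 0.5 the variance ratio is (0.352/0.321)² = 1.20, so the rule gives about 20% more variance. At r = 0.3 it is (0.362/0.354)² = 1.05, and at r = 0.7 it is (0.343/0.267)² = 1.65. Because baseline cotinine is already adjusted for, r here should be read as the correlation that remains after that adjustment.

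**5. If the choice is left open.** If either the adjusted or the unadjusted result could be reported, whichever is significant, type I error with one covariate reaches 6.3%, 7.1% and 8.3% for the three values of r. This is a worst case, not a prediction.

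**The case against.** The other side has several sound points.

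- **Adjustment is not solely conditional.** A reader might infer that covariates enter only when the arms look unbalanced. The text does not support that: individual covariates and baseline cotinine are adjusted for without condition, and baseline cotinine is probably the strongest predictor. This stands.
- **There is no contradiction between the two adjustment statements.** A reader might also infer that adjusting for baseline cotinine whatever its balance conflicts with the balance rule. It does not. The rule says that unbalanced factors go in; it does not say that balanced ones stay out. This stands.
- **No significance test is named.** The 0.75 SD and 0.26 SD thresholds, and any statement that large imbalances would be missed, hold only if balance is judged by a 5% test. If it were judged by the size of the difference, those figures would not apply. This stands. The 17% frequency of differences above 0.5 SD does not depend on a test.
- **Overall type I error is not inflated.** A reader might expect that it is. Averaged over allocations it is 3.7% to 4.7% in the simulation. Selection uses baseline variables, so it need not depend on outcomes. If ten independent factors were each tested at 5%, at least one would be flagged in 1 − 0.95¹⁰ = 40% of trials, but adjusting for a flagged baseline variable is not itself an error. This stands.
- **Naming covariates is often left to the SAP, which is not shown.** That is so, and the missing list alone would be no finding. But the article states a selection rule, and an SAP that followed it would inherit the fault.
- **The rule is confined to key variables and relevant factors.** That is some restriction, but neither term is defined, so relevance can be decided after the arms have been compared.

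**Conclusion.** The point holds in a limited form. For factors other than baseline cotinine and the unnamed individual covariates, the article selects adjustment by observed imbalance, which is the wrong criterion in a randomised trial, and leaves the trigger undefined. Imbalance above 0.5 SD in a given cluster-level factor is not rare under this design (about 17% of allocations).

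The harm is of three kinds:

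- **Lost precision:** about 20% more variance at r = 0.5, with a range from 5% at r = 0.3 to 65% at r = 0.7.
- **Conditional error:** 6.3% to 12.3% when an imbalance above 0.5 SD goes unadjusted.
- **An open choice of primary model.**

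The first two rest on the assumed 5% test, a single covariate analysed on cluster summaries, and assumed correlations; their size in this trial is unknown. The randomised comparison itself is not invalidated, and neither a false-positive rate above 5% on average nor an internal contradiction should be claimed.

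**What to change.** In Outcomes and estimation, replace the balance-triggered rule with a short covariate list that is fixed before allocation and used whatever balance is observed:

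- baseline cotinine of the same person, as the analysis bullets already provide;
- urban or peri-urban location;
- a few prognostic factors already collected, for example cluster size, number of rooms, and exposure to second-hand smoke outside the home.

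Keep the list short, because there are only 30 clusters. State that this list also replaces the unnamed individual covariates, so that a single covariate set produces the primary result. Show baseline tables descriptively, and label any adjustment prompted by observed imbalance as a sensitivity analysis.

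The cost is wording, plus a few degrees of freedom spent on cluster-level covariates. No new data are needed and the sample size is unchanged. As the article describes the trial, there is still time: Study status reports that baseline collection is ongoing, and allocation follows the baseline survey.
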